### Intervention protocol

2.3

The intervention integrates home-RAT with scheduled clinic visits across 3 phases over 24 weeks including an 8-week interventions phase and 16-week follow-up phase. Written informed consent will be taken from all eligible participants prior to enrolment. Refer to Figure 1 for the study protocol for all 3 hospitals.

**Figure 1 fig1:**
[figure not shown]
Study protocol.

#### Phase 1: onboarding and installation (week 0)

2.3.1

Visit 1 (clinic): baseline assessments, initial H-Man orientation and training, supervised 1:1 by rehabilitation therapist (90 min)Visit 1.1 (home): device installation by industry vendor, H-Man set up by rehabilitation therapist, programme setting and caregiver training on H-Man operations, safe mode of operation, troubleshooting with company FAQs (120 min)

#### Phase 2: treatment (weeks 1–8)

2.3.2

Home training (weeks 1–4, total 28 days): daily self-directed H-Man therapy, gradually increasing from 30 min per day during the first three days to 60 min by Day 4, and up to 120 min (with mandatory rest breaks every 30 min) from Day 7 onward, based on a standardized progression protocol. Escalation decisions are guided by predefined criteria: absence of increased pain (VAS increase ≤2 points), fatigue rated ≤6/10 on a self-reported scale, and no adverse events in the preceding sessions. The treating therapist reviews cloud-uploaded performance data weekly during telemonitoring calls and may recommend maintaining, increasing, or reducing duration. Participants are instructed not to exceed 120 min per day, caregiver supervision as needed. Participants were encouraged to increase training duration by repeating the prescribed games as tolerated, if no adverse effects such as arm pain or fatigue or increased muscle tone were noted. Similarly, participants had the option to reduce training duration per session/daily episodes or take breaks when needed. Therapists could remotely adjust or modify prescribed gameplay exercises or difficulty. Weekly remote monitoring was supplemented by phone calls as needed and in person checks during COT sessions.Telemonitoring: weekly 15-min therapist review of cloud-uploaded performance data with phone consultations if non-compliance or overexercise or variable performance are noted.Conventional therapy: four 60-min sessions at fortnightly intervals, conducted by rehabilitation therapist, during 8 weeks (2 sessions during home-RAT phase and 2 sessions after the home-RAT phase)Assessments: mid-treatment post-home-RAT (Week 6) and post-COT/end-treatment (Week 8) by occupational therapists or trained assessors.

#### Phase 3: follow-up (weeks 9–24)

2.3.3

Assessments: week 12 and 24 to evaluate sustainability of gains

All formal outcome assessments (baseline, Week 6, Week 8, Week 12, and Week 24) are conducted in-clinic at the respective study sites by the designated assessor, ensuring standardized testing conditions and access to calibrated equipment (e.g., Jamar dynamometer). The in-clinic setting also facilitates clinical safety review at each assessment timepoint (see Table 2).

**Table 2 tab2:** Intervention schedule and assessment timeline.

Week	0	1–4	6	8	12	24
Phase	Onboarding	Home Training	Mid-Treatment	End-Treatment	Follow-up	Follow-up
H-MAN Training	Training	Daily 60–120 min	Continued	Complete	-	-
Conventional occupational Therapy (COT)	-	2 sessions, fortnightly intervals	1 session	1 session	-	-
Telemonitoring	-	Weekly x4	-	-	-	-
Assessments (total 5)	Baseline	-	Primary	Secondary	Maintenance	Long-term

To ensure consistency and minimize bias, each site designates a primary treating therapist responsible for all enrolled participants at that site, including onboarding, telemonitoring, and conventional therapy sessions. Outcome assessments are conducted by a separate trained assessor at each site who is not involved in treatment delivery, thereby maintaining blinding to treatment progress. All assessors undergo centralized training using standardized assessment protocols and video calibration sessions prior to study commencement, with inter-rater reliability established at >0.85 (ICC) for FMA-UE and ARAT.

### H-Man system specifications

2.4

The H-Man robot’s design philosophy prioritizes clinical functionality and home deployment feasibility over technological complexity, achieving a balance that addresses key implementation barriers while maintaining therapeutic effectiveness. Technical specifications were optimized through iterative development with stroke survivors and therapists, ensuring the system meets clinical requirements for motor relearning while remaining accessible for home use. The device’s compact form factor, intrinsic safety features, and simplified operation enable deployment in diverse home environments without specialized infrastructure or technical expertise. Carers can be trained for independent operations of H-Man, and Wi-Fi is not essential for operations. Data upload to cloud occurs with adequate Wi-Fi bandwidth.

Table 3 presents detailed technical parameters alongside their clinical relevance for stroke rehabilitation.

**Table 3 tab3:** H-MAN technical specifications.

Parameter	Specification	Clinical Relevance
Physical		
Weight	14 kg	Caregiver portable
Dimensions	880 × 700 × 400 mm	Standard table compatible
Workspace	400 × 300 mm planar	Functional reach range
Mechanical		
Degrees of Freedom	2 active (x,y)	Planar reaching/drawing
Transmission	H-cable differential	Intrinsic safety
Force Capacity	50 N maximum	Therapeutic resistance
Control		
Sampling Rate	1,000 Hz	Smooth interaction
Impedance Control	0–50 N/m adjustable	Progressive assistance
Interface		
Display	15″ touchscreen	Clear visualization
Games	8 VR environments	Varied practice
Feedback	Visual + haptic + audio	Multimodal learning
Data		
Storage	32GB local + cloud	Offline capability
Connectivity	Wi-Fi (intermittent OK)	Flexible deployment

The H-Man robot is manufactured and distributed by Articares Pte Ltd. (Singapore), which provides device installation, technical maintenance, and replacement units under warranty this interests statement.

#### H-Man training protocol and therapeutic content

2.4.1

The H-Man training protocol comprises structured exergaming activities designed to promote repetitive, goal-directed upper limb movements within the planar workspace. Training targets three primary movement patterns: (a) point-to-point reaching in multiple directions, training shoulder flexion-extension and abduction-adduction with elbow coordination; (b) continuous tracing and drawing tasks requiring sustained smooth movement control; and (c) functional trajectory movements simulating activities such as wiping and reaching-to-grasp patterns.

The H-Man system provides three modes of robot-patient interaction: (i) active-assisted mode, where the robot supplements patient-initiated movement toward targets with adjustable impedance (0–50 N/m); (ii) active-resisted mode, providing resistance against patient movement to strengthen motor output; and (iii) free active mode, where the robot provides no assistance or resistance and serves only as a measurement instrument. Mode selection is prescribed by the treating therapist during onboarding based on baseline motor capacity and is adjustable during weekly telemonitoring reviews.

The exergaming interface offers eight virtual reality game environments displayed on the integrated 15-inch touchscreen, including target-hitting, path-following, maze navigation, and object-sorting tasks. Each game provides multimodal feedback: visual feedback (real-time cursor tracking, target highlighting, and score display), haptic feedback (force cues from the robot handle indicating target proximity and movement errors), and auditory feedback (tones for successful target acquisition and verbal encouragement). Game difficulty auto-adjusts based on performance metrics including movement accuracy, speed, and smoothness. The treating therapist may recommend specific games and interaction modes during telemonitoring to target individual impairment profiles (e.g., emphasizing reaching accuracy for patients with dysmetria, or resistance training for those with proximal weakness). Training is thus individualized within a standardized framework rather than applied as a uniform protocol.

### Outcome measures

2.5

#### Primary outcome

2.5.1

##### Utilization rate

2.5.1.1

Percentage of prescribed sessions completed (≥30 min/day active exergaming therapy without idling time was deemed as compliance/day), automatically captured via cloud monitoring. Success threshold ≥75% based on dose–response literature and based on prior validation trial for hospital-home-RAT.

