**Methods:**

This pragmatic, single-arm, multi-center prospective trial will recruit 54 adults with subacute to chronic stroke (>28 days post-event) with upper extremity impairment (Fugl-Meyer Assessment 10–60) across three tertiary rehabilitation centers in Singapore. The intervention comprises four weeks of intensive home-based, caregiver-supervised training using the H-Man robot (60–120 min daily) with weekly telemonitoring, combined with four conventional occupational therapy sessions over an eight-week treatment period. The primary outcome is utilization rate (≥75% compliance) measured by cloud-based metrics. Secondary outcomes include motor impairment (FMA-UE), functional capacity (ARAT), quality of life (EQ-5D-5L), usability (System Usability Scale), and technology acceptance, assessed at baseline, 6, 8, 12, and 24 weeks. Economic evaluation will assess cost-effectiveness from healthcare system and societal perspectives.

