Comprehensive economic evaluation provides crucial evidence for policy decisions in resource-constrained health systems facing a growing stroke burden. If home-RAT demonstrates comparable clinical effectiveness at lower total societal cost, the value proposition becomes compelling for health system transformation. The inclusion of willingness-to-pay assessment captures patient preferences and perceived value often overlooked in technology adoption decisions but critical for sustainable implementation and appropriate pricing strategies. Success could catalyze multiple policy changes including development of regulatory frameworks for home-based rehabilitation technology, quality standards for remote monitoring and supervision, reimbursement models covering technology-enabled care.

Several limitations warrant consideration when interpreting results. The single-arm design, while pragmatic and ethically justified given existing robust evidence, limits causal inference compared to randomized controlled trials, though comparison with robust historical controls and sensitivity analyses partially address this limitation. The 24-week follow-up may miss important long-term outcomes occurring years after stroke, including durability of gains, and technology abandonment, though cloud performance tracking. Technology requirements including basic internet connectivity and smartphone access may exclude digitally disadvantaged populations, potentially exacerbating health disparities despite efforts to minimize technical barriers through simplified interfaces and comprehensive training. The requirement for stable home environments and available caregivers may exclude vulnerable populations including those living alone or in institutional care, limiting generalizability to those potentially most needing innovative rehabilitation solutions.

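### The primary utilization rate is read from the cloud alone, so completed days on a device that never syncs would look like non-use

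*Protocol article*

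**What the plan says.** Section 2.5.1.1 (Utilization rate) defines the primary outcome as "Percentage of prescribed sessions completed (≥30 min/day active exergaming therapy without idling time was deemed as compliance/day"), and says that it is "automatically captured via cloud monitoring". The Methods paragraph of the abstract agrees: "The primary outcome is utilization rate (≥75% compliance) measured by cloud-based metrics". Neither place names a second source.

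Section 2.4 (H-Man system specifications) describes a device that does not depend on a connection: "Wi-Fi is not essential for operations", and "Data upload to cloud occurs with adequate Wi-Fi bandwidth". Table 3 in that section lists storage as "32GB local + cloud", which it links to offline use, and accepts intermittent Wi-Fi.

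Table 1 (eligibility) requires a stable home and a caregiver but says nothing about internet access. The limitations paragraph of the Discussion points the other way: "Technology requirements including basic internet connectivity and smartphone access may exclude digitally disadvantaged populations".

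During treatment, section 2.3.2 provides a "weekly 15-min therapist review of cloud-uploaded performance data", with a phone call if use looks too low, too high or erratic.

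Section 2.7 (Statistical analysis plan) assigns zero utilization to the remaining sessions of participants who withdraw. It gives multiple imputation as the general method for missing data. Neither rule mentions sessions that were completed but not uploaded.

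**The concern.** The denominator of the rate is prescribed sessions. The numerator is whatever the cloud has captured. Where the two stated facts about the device meet, that is, training possible offline and upload conditional on bandwidth, a participant can complete a day that never enters the numerator. In the cloud record that day looks the same as a day on which the robot was not switched on.

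The analysis rules do not separate the two. The zero rule covers withdrawals only. Imputation needs to know which days are missing, and the cloud feed alone cannot show this.

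The stated primary objective is to determine this rate as a guide to whether home delivery is viable. If some homes do not sync, the rate mixes adherence with home connectivity, and the error runs in one direction. The per-protocol set (at least 75% of sessions completed) and the dropout definition (unable to complete half of the home phase) also rest on session completion. They would inherit the error if they are read from the same record.

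**Working it through.** **Inputs.** Benchmark 70%, margin 5 points and 54 participants (section 2.2.2); limit 65% (section 2.7); 28 training days (section 2.3.2); about 50 MB uploaded per session (section 2.6); 32 GB local storage (Table 3). The share of completed days that never reach the cloud, called f here, is not in the documents and is assumed over a range.

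**1. The plan's own figure.** 70% − 5 points = 65%, which matches the limit in section 2.7.

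**2. Can the device hold the whole record?** Taking the upload size as the storage size, 32,000 MB / 50 MB = 640 sessions. At one session a day the home phase needs 28 × 50 MB = 1.4 GB. At an assumed four a day it needs 28 × 4 × 50 MB = 5.6 GB. Capacity is not the limit. A completed day is lost only if the local data are never uploaded and never read from the device.

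**3. Effect on the rate.** Observed rate = true rate × (1 − f). The loss that brings the point estimate to 65% is f = 1 − 0.65 / true rate.

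- True 70%: 1 − 0.65/0.70 = 7.1%. Completed days per participant average 28 × 0.70 = 19.6, so this is 19.6 × 0.071 = 1.4 days each.
- True 75%: 1 − 0.65/0.75 = 13.3%.

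| Assumed f | Observed if true 70% | Observed if true 75% |
|---|---|---|
| 2% | 68.6% | 73.5% |
| 5% | 66.5% | 71.25% |
| 10% | 63.0% | 67.5% |
| 20% | 56.0% | 60.0% |

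**4. The same in whole devices.** Loss is more plausible as a few devices that never sync than as a little from every home. Suppose such participants have average use. Three of 54 give 70% × 51/54 = 66.1%, and four of 54 (7.4%) give 70% × 50/54 = 64.8%.

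**5. What these figures are not.** They compare a point estimate with 65%. Section 2.7 requires the lower confidence limit to exceed 65%, so a trial could fail at a smaller loss than those in step 3. How much smaller depends on the spread of utilization between participants, which the article does not give. The figures show sensitivity only. They do not predict the trial's result.

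**The case against.** The strongest reply is that no sentence scores an un-uploaded day as non-use. A reader might infer such a rule from the cloud-only definition, but the only stated zero rule concerns withdrawals. This is correct, and the point does not depend on an explicit rule: if the cloud is the source, a session it lacks is not counted.

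Second, local storage and the acceptance of intermittent Wi-Fi suggest that sessions are held and uploaded later. This stands. Ordinary outages probably cost nothing, and the risk is confined to devices that never sync before the rate is computed.

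Third, a reader might infer that the error falls mainly on digitally disadvantaged homes. The documents do not support that, because the Discussion says that such people may be excluded. What remains is a tension: Table 1 does not require internet, section 2.4 says the robot works without Wi-Fi, and the Discussion lists connectivity as a requirement.

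Fourth, it is tempting to say that remote review is blind to these homes. That goes too far. An empty feed would look like non-compliance and prompt a call, and two conventional therapy visits fall within the home phase. These contacts could reveal a sync failure, but the article states no step by which the endpoint is then corrected.

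Fifth, one might expect distorted site or subgroup comparisons. None is planned for utilization; the subgroup analyses use the mixed models for clinical outcomes.

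Sixth, the bias is downward and so cannot by itself produce a false claim of non-inferiority. This is true, but an understated rate still misinforms a trial whose purpose is to measure it.

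Finally, log retrieval is an operational detail that the full protocol may contain. That is fair, and the absence of a retrieval procedure is not the point. The article does fix the data source, and that source does not fit the device's stated way of working.

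**Conclusion.** The point holds in a limited form. The primary outcome is tied to cloud capture alone, while the device may be used offline and eligibility does not require internet. For devices that never sync, completed days drop out of the numerator and cannot be distinguished from non-use, so utilization is biased downward.

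The amount cannot be estimated from the documents. It is zero if every device eventually syncs. On the illustrative scale, a loss of 7.1% of completed sessions, or about four never-synced devices among 54 participants with average use, brings a true 70% point estimate to about 65%. This rests on an assumed loss share and on un-captured days going uncounted.

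The documents do not support saying that completed sessions are being lost, or that poor Wi-Fi as such loses them. The point is worth correcting because the margin is narrow and the remedy is cheap, but it does not undermine the design.

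**What to change.** In section 2.5.1.1, and correspondingly in the abstract, define utilization from the device's local session log. Download or force-sync the log when the device is retrieved, and reconcile it with the cloud record before the rate is computed. Count a day as compliant if either record shows at least 30 active minutes. Keep the cloud feed for interim monitoring.

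Leave all other days under the intention-to-treat rule of section 2.7. Report days with no record because of device failure separately, as a sensitivity analysis. Removing them from the primary rate would be debatable, since technical failure is part of what an implementation endpoint should capture.

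Also state whether home internet is required, so that Table 1, section 2.4 and the Discussion agree.

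The cost is a sentence or two of text and one log download per device. The change assumes that the device keeps its sessions until it is collected, which the sponsor should confirm. Recruitment began in October 2024, so this should be settled before devices are cleared or reissued, and the report should say for how many participants a local log was available.

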#### Secondary outcomes

2.5.2

##### Motor and functional

2.5.2.1

Upper extremity (UE) Fugl-Meyer Motor Assessment (FMA) is a widely used quantitative measure of motor impairment to evaluate upper-limb recovery. Its scores range from 0 being the minimum to the maximum score of 66 points and is divided into UE including shoulder-elbow, and coordination and speed (0–42) and distal wrist-hand scores (0–24).Action Research Arm Test (ARAT) is a 19-item observational measure of upper-extremity performance score and score ranges from 0 being the minimum to the maximum score of 57 points. It consists of 4 sub-tests (grasp., grip, pinch, and gross movement). Each task performance is rated on a 4-point scale ranging from 0 (no movement) to 3 (normal movement). The subscale ranges for each subtest are grasp (6 items, 0–18), grip (4 items, 0–12), pinch (6 items, 0–18) and gross movement (3 items, 0–9). Scores from each task are summed, with a minimum total score of 0 to a maximum score of 57.Affected hand grip strength is measured using Jamar Dynamometer (kg) using the mean reading of 3 attempts.Clinical measures of hemiparetic limb spasticity of shoulder adductors, elbow flexors, wrist and finger flexors using the Modified Ashworth Scale scores (MAS)Visual Analogue Scale: Pain assessment of shoulder and arm (0–10)

##### Quality of life and participation

2.5.2.2

EQ-5D-5L: health utility for economic analysisPROMIS-10: global health statusStroke impact scale-16: stroke-specific quality of life

##### Technology acceptance

2.5.2.3

System usability scale: perceived usability (0–100, >68 acceptable)Intrinsic motivation inventory: engagement and perceived valueTechnology acceptance model: intention to continue use

##### Economic

2.5.2.4

Direct medical costs: device, therapy time, clinic visitsDirect non-medical costs: transportation, caregiver timeIndirect costs: productivity lossesWillingness-to-pay: contingent valuation

### Data collection and management

2.6

The study employs multi-modal data collection through standardized clinical assessments by trained assessors (inter-rater reliability >0.85), secure REDCap database with validation rules and audit trails, automated cloud upload of robotic performance data (100 Hz sampling, ~50 MB/session), and structured medical record abstraction with double data entry for critical variables. Comprehensive data security includes AES-256 encryption for all transmissions, Singapore-based servers for data residency compliance, role-based access with two-factor authentication, and complete participant de-identification with separate storage of linking files. The H-Man system contains no identifiers, using only study IDs, with all data retained for 6 years per institutional requirements before secure destruction.

### Statistical analysis plan

2.7

The primary analysis evaluates non-inferiority of the observed utilization rate against a 70% historical benchmark derived from clinic-based RAT programs, with a pre-specified non-inferiority margin of 5%. Non-inferiority is demonstrated if the lower bound of the one-sided 95% confidence interval for the observed utilization rate exceeds 65%. This analysis follows intention-to-treat principles, including all enrolled participants regardless of completion status; participants who withdraw are assigned zero utilization for remaining sessions.

For secondary clinical outcomes (FMA-UE, ARAT, grip strength, EQ-5D-5L, SIS-16, PROMIS-10), linear mixed-effects models are employed with fixed effects for time (categorical: baseline, Week 6, Week 8, Week 12, Week 24), site, and baseline severity (FMA-UE score), and a random intercept for participant to account for within-subject correlation across repeated measures. An unstructured covariance matrix is specified, with model fit compared against compound symmetry using the Akaike Information Criterion. The assumption of normally distributed residuals will be assessed using Q-Q plots and the Shapiro–Wilk test; non-normal outcomes will be analysed using generalized linear mixed models with appropriate link functions. Multiple comparisons across secondary outcomes are controlled using the Benjamini-Hochberg False Discovery Rate procedure at q = 0.05.

Exploratory subgroup analyses examine treatment effect heterogeneity by stroke chronicity (<6 months vs. ≥6 months), baseline severity (FMA-UE < 30 vs. ≥30), age (<65 vs. ≥65 years), and cognitive status (MoCA 21–25 vs. >25) using interaction terms in the mixed models. These are hypothesis-generating and interpreted cautiously given the sample size.

The economic evaluation calculates incremental cost-effectiveness ratios (ICERs) comparing total costs of the TRUST intervention against usual care (historical cost data), with effectiveness expressed as quality-adjusted life years (QALYs) derived from EQ-5D-5L utility scores. A 12-month Markov model with three health states (independent, dependent, deceased) is constructed, with transition probabilities informed by observed clinical trajectories and published literature. Costs and QALYs are discounted at 3% per annum. Uncertainty is characterised through probabilistic sensitivity analysis using 10,000 Monte Carlo simulations with parameters drawn from appropriate distributions (gamma for costs, beta for utilities, log-normal for relative effects), presented as cost-effectiveness acceptability curves against Singapore-specific willingness-to-pay thresholds. Missing data are handled using multiple imputation by chained equations under the missing-at-random assumption, with sensitivity analyses under missing-not-at-random scenarios.

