#### Sample size calculation

2.2.2

Sample size determination used non-inferiority framework with utilization rate as primary outcome. Based on 70% utilization in clinic-based programs (historical controls) and 5% non-inferiority margin, 18 participants per site (*n* = 54 total) provides 80% power at *α* = 0.10 (one-sided). This sample accounts for an anticipated 15% dropout rate (approximately 8 participants), yielding a minimum evaluable sample of 46 participants. Dropout is defined as withdrawal of consent, loss to follow-up, or inability to complete ≥50% of the home-RAT phase. Sensitivity analyses will compare intention-to-treat (all enrolled) and per-protocol (≥75% session completion) populations.

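### The primary rule declares home use non-inferior to a 70% clinic figure that nothing in the article puts on the trial's own definition of utilization

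*Protocol article*

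**What the plan says.** Three parts of the protocol article define the home side.

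- Section 2.5.1.1 defines the outcome as a percentage of prescribed sessions, captured by cloud monitoring, with the daily criterion "≥30 min/day active exergaming therapy without idling time was deemed as compliance/day".
- Section 2.3.2 sets the period and frequency: "Home training (weeks 1–4, total 28 days): daily self-directed H-Man therapy". The prescribed duration rises, "gradually increasing from 30 min per day during the first three days to 60 min by Day 4, and up to 120 min".
- Section 2.7 analyses all enrolled participants and scores sessions after withdrawal as zero.

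The reference side is a single figure. Section 2.2.2 has "Based on 70% utilization in clinic-based programs (historical controls) and 5% non-inferiority margin", and section 2.7 has "The primary analysis evaluates non-inferiority of the observed utilization rate against a 70% historical benchmark derived from clinic-based RAT programs". The decision rule in section 2.7 is "Non-inferiority is demonstrated if the lower bound of the one-sided 95% confidence interval for the observed utilization rate exceeds 65" per cent.

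The design is single-arm (section 2.1). The limitations paragraph of the Discussion describes the historical controls as robust and counts on them to offset part of that limitation. Section 2.5.1.1 also sets a separate success threshold of 75%, which it attributes to dose–response literature and a prior hospital-home trial.

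**The concern.** A non-inferiority margin is a permitted difference between two values of the same quantity. Here one value comes from a rule written for this trial: non-idle minutes logged by the device, a 30-minute cut-off, a daily prescription over 28 days, and zeros after withdrawal. The other is a fixed percentage from clinic programmes. The article does not say that it counts the same thing, and it does not argue that the two measures are comparable.

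This is the primary analysis, and there is no concurrent group to anchor it. If the bound clears 65%, the stated rule yields a comparative conclusion about clinic-based therapy. That conclusion depends on the 70% being the clinic value on the home rule. If it is not, the effective margin is not 5 points, and nothing in the trial data would show it.

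**Working it through.** **Step 1. The plan's own figure.** Benchmark 70% minus margin 5 points gives 70 − 5 = 65%, the bound in section 2.7. The arithmetic is right. It takes the 70% as already on the home scale.

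**Step 2. The two sides compared.**

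| Element | Home rate | 70% benchmark |
|---|---|---|
| What counts | at least 30 active, non-idle minutes in a day | not stated |
| Denominator | prescribed daily sessions, 28 days | not stated |
| Data source | device log, cloud | not stated |
| Withdrawals | zero for remaining sessions | not stated |

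The possible biases run both ways. The non-idle requirement and the zeros for withdrawals make the home rule stricter than plain attendance. The cut-off makes it more lenient than completing a full session: once 60 to 120 minutes are prescribed, 30 minutes is 30/60 = 50% down to 30/120 = 25% of the day's dose. The direction is therefore open.

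**Step 3. Sensitivity of the margin, by assumption.** The documents give no clinic rate on the home rule, so these figures are illustrations.

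(a) Suppose 70% is attendance, and a share q of attended sessions would meet the active-minute rule. The matched benchmark is 70 × q, the matched bound is 70 × q − 5, and the margin actually applied by a 65% bound is 70 × q − 65.

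| q | Matched benchmark | Matched bound | Margin applied by 65% |
|---|---|---|---|
| 1.00 | 70.0% | 65.0% | 5.0 points |
| 0.95 | 66.5% | 61.5% | 1.5 points |
| 0.90 | 63.0% | 58.0% | −2.0 points |
| 0.85 | 59.5% | 54.5% | −5.5 points |
| 0.80 | 56.0% | 51.0% | −9.0 points |

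Below q = 65/70 = 0.93 the rule asks home use to exceed clinic use.

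(b) Suppose instead that clinic programmes would score c on the home rule, for instance because the 70% used a stricter criterion for completion. The deficit tolerated is c − 65: for c = 75%, 80% and 85% it is 10, 15 and 20 points.

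**Step 4. What this does to the decision.** Treat the rate as a mean of participant percentages with n = 54, and assume an SD of 20 to 30 points (no SD is given). The probability of passing is Φ((true − 0.65) × √54 / SD − 1.645).

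- If clinic is 63% on the home rule and home use is equal to it, the probability of passing is 0.9% (SD 20) to 1.6% (SD 30).
- If clinic is 80% on the home rule and home use is 75%, exactly on a true 5-point margin, the probability is 97.9% (SD 20) down to 78.9% (SD 30). A correctly placed bound would give 5%.

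The sample size and its stated α of 0.10 are separate matters. Here 54 serves only as n, and 1.645 comes from the 95% bound in section 2.7.

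**The case against.** The strongest reply is that the mismatch is inferred. The article does not say how the 70% was measured. Because it comes from robot-therapy programmes, device-logged active time is as open a possibility as attendance. A condensed article may also leave the source and definition of a benchmark to the full protocol. This stands: the lack of detail is not the complaint, and no mismatch is demonstrated. What remains is the conclusion that the article itself fixes, which is non-inferiority declared on a measure specified narrowly for one side only.

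A reader might infer more than the documents support, in three ways.

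- That daily home training against fewer booked clinic days shifts the percentage by itself. It does not. Utilization is the share of each programme's own prescribed sessions, so full completion is 100% in either. Differences in sessions per week are differences in dose, which this outcome does not measure.
- That a participant training on fewer than 65% of days fails the rule. The 65% applies to the lower bound of the group rate and is no cut-off for one person.
- That the clinic figure is known to be attendance on a non-daily schedule. Section 1.2 describes sparse outpatient sessions, and section 1.5 says that current care cannot provide daily intensive rehabilitation. Both concern general care and do not say how the 70% was counted.

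It is also fair that the article's conclusions do not claim parity with clinic utilization, and that the Discussion concedes the limits of a single arm. The decision rule and the reliance on historical controls still stand in the text.

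**Conclusion.** The concern holds in a limited form. The test in section 2.7 is a valid comparison of one observed rate with a fixed 65%. Reading a pass as non-inferiority to clinic-based robot therapy requires the 70% to be on the definition in section 2.5.1.1, and nothing in the article establishes that. The size and direction of any discrepancy cannot be determined.

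Under the stated assumptions, the matched bound could lie at 51–61.5% (q from 0.80 to 0.95), or a 65% bound could tolerate a deficit of 10–20 points (clinic at 75–85% on the home rule). Mismatches of this size would take up most of a 5-point margin or exceed it. These ranges show how fragile the margin is. They do not estimate bias, and they do not show that the benchmark is wrong. The change should be made, because it alters what the primary result may be said to show.

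**What to change.** In sections 2.2.2 and 2.7, describe the primary analysis as a single-arm test of the observed utilization rate against a fixed performance goal of 65%, met if the one-sided 95% lower bound exceeds it. State that no conclusion of non-inferiority to clinic robot therapy will be drawn. In section 2.2.2, drop the description of the 70% as historical controls. In the Discussion's limitations paragraph, remove or qualify the description of those controls as robust.

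Keep a clinic comparison only if the 70% is shown to follow the section 2.5.1.1 rule, or is recomputed from source data on that rule with withdrawals handled in the same way. Even then, present it descriptively.

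The relabelling changes wording only: the bound and the data collection stay as they are. There are two costs. The headline claim becomes more modest. And because 65% is now justified only as 70 minus 5, it will need its own stated rationale as a goal, including how it relates to the 75% success threshold. Recomputing the benchmark would need access to source data and is optional.
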